### Eligibility criteria

#### Inclusion criteria

People aged 18 years or over.Diagnosis of HNC with requirement for a neck dissection as a part of their treatment with curative intent, Including those undergoing completion neck dissection following positive sentinel node biopsy or open neck node biopsy.Able to attend outpatient physiotherapy appointments.Provide informed consent.

#### Exclusion criteria

People for whom intensive postdischarge physiotherapy is expected (eg, scapula/scapula tip and/or latissimus dorsi free flaps or components thereof). This constitutes 3%–5% of the neck dissection population, and clinical equipoise regarding the role of physiotherapy is less evident.^21^People with a pre-existing, long-term disease affecting the shoulder, for example, hemiplegia.People who had prior neck dissection surgery on the affected side.People undergoing only lymph node biopsy or sentinel lymph node biopsy.Previous entry in the present trial.Unable to adhere to trial processes.

N.B. Patients who have been excluded from the trial due to meeting exclusion criteria 4 may subsequently become eligible for inclusion *if* they require complete neck dissection.

### Participant identification, screening and withdrawals

As a part of a potential participant’s surgical multidisciplinary care outpatient appointment, and after the treatment plan has been discussed when they have been identified as requiring neck dissection, they will be approached, and if willing, screened for eligibility. Participants may also be approached in their preoperative assessment clinic or when admitted for surgery. Consent must be obtained preoperatively. Eligibility can be assessed by routine clinical evaluation, with no requirement for any specific investigation. Screening data will be entered directly on to the GRRAND trial bespoke database.

Patients who are eligible will be given verbal and written information (either in person, by post or email) about the trial and invited to discuss it further with a member of the research team. They will be given adequate time to consider participation. A delegated member of each local research team will obtain informed consent (written consent or witnessed remote verbal consent) from each participant. This will be sought preoperatively. However, following surgery, participants’ eligibility will then be verified by reviewing the medical/surgical notes. Baseline data will be collected once consent is obtained and prior to surgery.

### Randomisation and blinding

Participants will be randomly allocated to the two treatment groups via a central computer-based randomisation system provided by WCTU’s programming team, independent of the study team. This will be performed after consent has been obtained and he baseline data have been collected.

Randomisation will use a variable block size and will be 1:1 using minimisation, stratified by: age (<60 years vs>=60 years); hospital site and spinal accessory nerve sacrifice (yes/no). Randomisation will be performed by any delegated member of the local clinical or research team, using the online system.

Due to the participatory nature of rehabilitation, it is not possible to blind participants to group allocation. However, trial team members who collected or inputted data to the database will be blinded to group allocation.

### Trial treatment(s)/interventions

#### Group 1: GRRAND physiotherapy programme

A template for intervention description and replication checklist^36^ for the GRRAND intervention is included as online supplemental file 4. The development of this has been previously reported.^23^

*Delivered by:* physiotherapists trained in the principles of the GRRAND programme. Training includes background to the problem, the rationale for the trial, an overview of the GRRAND framework and trial documentation. Trained physiotherapists receive a GRRAND manual containing a detailed account of trial and intervention procedures.

*Mode of delivery:* the intervention will be personalised to the participant, allowing for flexibility for GRRAND to be delivered face-to-face in physiotherapy departments, through virtual consultations, or a hybrid of the two.

*Treatments:* participants randomised to the experimental group will receive the control group (inpatient) intervention PLUS a personalised physiotherapy-led intervention (the GRRAND programme) comprising up to six, 1-hour outpatient appointments (first session aimed for within 14 days posthospital discharge) over 6 months.

Physiotherapy treatment will include the following options.

*Range of motion exercises* targeting muscles and joints of the neck and shoulder impacted by neck dissection. Participants will be taught stretching and joint range of motion exercises for shoulder and neck.*Progressive resistance exercises* targeting strengthening of the neck and shoulder girdle, and prevention of the onset of adhesive capsulitis. The resistance exercises will target the stabilising functions of the upper quadrant and movements of shoulder internal rotation, external rotation and abduction. Exercises will be progressed through increasingly elevated shoulder positions and the introduction of weight bearing through the upper limb. Additionally, the exercises will become increasingly ‘task specific’, targeting the specific functional goals and usual activities of daily living of the participant. Resistance loads (using resistance bands) will initially be set at a moderate level of exertion (determined by a combination of physiotherapist observation and participant-reported exertion based on the modified Borg scale of perceived exertion^37^) to permit progression, enhance motivation and adherence and reduce the possibility of symptom flare-up. Progression will be achieved by increasing the resistance load, speed and/or the number of repetitions and sets of exercises.*Continued education and advice on positioning, oral health and pain management*, based on the GRRAND manual provided to participants at discharge.*Education and advice on optimising exercise adherence and return to function*. This will be targeted in two ways: first, through the introduction of behaviour techniques of goal setting, pacing, behaviour modification, graded activity and for reducing fear avoidance; and second, through the discussion of barriers and facilitators to exercise and activity participation.^38^ Physiotherapists will promote independence and confidence in returning to normal activities of daily living, occupational and social pursuits and problem solving the physical neck and shoulder challenges with participants. The programme will use an established, effective approach to introduce these behaviour change techniques,^39^ developed from our previous clinical trials,^40 41^ which is within the current scope of practice for physiotherapists to deliver.*Education and psychological support to address fatigue, anxiety and sleep hygiene*. Due to the high prevalence of psychological health issues postoperatively, participants will be offered strategies to support self-management of fatigue, anxiety and sleep.

*Personalised tailoring*: at the initial consultation, a physiotherapist will assess the participant to identify modifiable physical and psychosocial factors associated with poor recovery after neck dissection. The participant’s personalised GRRAND programme is based on a combination of clinical assessment and participant-identified preferences.

*How and when:* the experimental intervention will be received by participants up to six times (one assessment; five follow-up appointments) over a 6-month period to facilitate supported recovery. Reflecting the heterogeneity of clinical presentation and need, if clinically indicated, participants will be permitted to receive additional sessions over a longer duration within the trial. Nonetheless, our feasibility study results^23^ and clinical advisory group indicated that anticipated treatment should be completed within the six sessions/6-month parameters.

Reflecting normal NHS practice, the initial assessment will be 60 min as a face-to-face session. Follow-up sessions will be up to 60 min in duration, either face-to-face or virtual. The timing and mode of delivery are flexible to account for ongoing treatment, physiotherapist judgement and participant preference. Participants will be asked to perform a regular home exercise programme, for example, at least three times a week for 20–30 min.

#### Group 2: usual postoperative care

There is currently no standard treatment across the UK for rehabilitation following neck dissection for HNC.^21 42^ Accordingly, we consulted with the Clinical Advisory Group and the findings from our national survey^21^ and feasibility study^23 43^ to ensure the content and delivery of a usual practice intervention for this patient group reflects usual, NHS care.

The ‘usual care’ is based around the following four areas.

Advice to practise simple range of motion exercises for the face, neck and shoulder impacted by neck dissection, for the purpose of preventing the onset of postsurgical contracture and optimising the functions of swallowing and shoulder girdle movement.Respiratory care, targeting the functions of sputum clearance and breathing control.Mobility assessment to ensure safe hospital discharge.Education on body positioning to reduce pressure and drag on the shoulder girdle, oral health to reduce food pocketing in the mouth and pain management to optimise levels of comfort and function.

As a part of ‘usual care’ prior to hospital discharge, the ward physiotherapist will provide participants with a Hospital Discharge Booklet detailing postoperative, self-management strategies inline with the standards currently used in these settings. No routine outpatient or follow-up physiotherapy will be provided as per current, best, usual NHS care.^21^

### Concomitant recovery treatments

In accordance with the pragmatic nature of this trial, participants will not be asked to desist from receiving other forms of treatment during the trial or follow-up periods. These may include contact with their GP, physiotherapist or other health professional, changes in medication or use of alternative therapies or treatments. Use of these treatments will be recorded through the health utilisation questionnaire at each follow-up period. The frequency of participants in the control group receiving physiotherapy will be reported to the oversight committees.

### End of trial

The trial will end when the analysis of 12-month follow-up data is completed. The trial will only be stopped early if mandated by the Research Ethics Committee (REC) or sponsor, following recommendations from the Data Monitoring Committee (DMC) or TSC; or if funding for the trial ceases.

### Safety reporting, AEs and SAEs

All AEs and SAEs will be defined using widely accepted standard criteria. For this trial, AEs and SAEs will be collected from the point of randomisation up to 12 months. SAEs will be reported to WCTU within 24 hours of research staff becoming aware of the event. These will be followed up until they are resolved, or until the end of the trial, and an outcome has been agreed.

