#### Secondary objectives

To evaluate postoperative pain, function, HRQoL, mental well-being, resource use and AEs at the following timepoints after randomisation based on:

SPADI total score and pain and disability domains at 6-weeks and 6-months postrandomisation.^25^EORTC (European Organization for Research and Treatment of Cancer) cancer-specific questionnaires (C30 (core))^26^ and H&N35 (head and neck specific)^27^ at 6-weeks 6- and 12-months postrandomisation.EQ-5D-5L^28^ at 6-weeks 3-, 6- and 12-months postrandomisation.Exercise adherence Rating Scale (EARS)^29^ at 6-weeks postrandomisation.Short Warwick–Edinburgh mental well-being scale (SWEMWBS)^30^ at 6-weeks 6- and 12-months postrandomisation.Health resource use questionnaire at 6-weeks 3-, 6- and 12-months postrandomisation.AEs and postoperative complications at 6-weeks 3-, 6- and 12-months postrandomisation.

To conduct a multimethods, process evaluation to examine trial processes, implementation fidelity and contextual factors are influencing delivery and engagement. This includes assessing mechanisms of impact, such as exercise adherence using the EARS,^29^ and synthesising quantitative and qualitative data to explore what works, for whom and in what contexts.

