#### Secondary outcomes

Secondary outcome measures are as follows:

SPADI total score^25^ at 6-weeks and at 6-months postrandomisation.SPADI total score^25^ for the pain and disability domains at 6-weeks 6-months and 12-months postrandomisation.EORTC QLQ-C30^26^ at 6-weeks 6-months and 12-months postrandomisation.EORTC QLQ-H&N35^27^ at 6 weeks, 6-months and 12-months postrandomisation.Mental well-being using the SWEMWBS^30^ at 6-weeks, 6-months and 12-months postrandomisation.Exercise adherence using the EARS^29^ at 6 weeks for both groups in addition to the last GRRAND physiotherapy appointment for those allocated to the GRRAND programme.EQ-5D-5L^28^ at baseline, 6-weeks, 3-months, 6-months and 12-months postrandomisation.Health resource use questionnaire at 6-weeks, 3-months, 6-months and 12-months postrandomisation.AEs and postoperative complications using the Clavien–Dindo Classification^35^ at 6-weeks, 3-months, 6-months and 12-months postrandomisation.

Process evaluation measures will include the number of staff trained, pre- and poststaff training knowledge and confidence with delivering structured HNC physiotherapy, the schedule and setting of session delivery (inpatient, outpatient or virtual), hospital and intervention case report forms (CRFs), including surgical procedure and spinal accessory nerve integrity, and observational checklists from site visits to assess fidelity.

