#### Safety outcomes

AEs and serious adverse events (SAEs) related to the trial postconsent will be recorded on the appropriate CRF for return to the Warwick Clinical Trials Unit (WCTU) Team and reported to the relevant oversight committees. Further surgery, apart from the index intervention, will be considered an outcome. Treatment AE or SAE related to concomitant care, such as chemo- or radiotherapy, will not be considered recorded AEs. Persistent pain without new pathology or another event will not be considered an AE, as it will be recorded in outcome scores. SAEs will be followed up until the end of the 12-month follow-up period. All AEs and SAEs will be managed in accordance with WCTU’s standard operating procedure (SOP).

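### Only the GRRAND arm has trial-delivered physiotherapy sessions at which adverse events can come to light, so the between-arm comparison can show an excess that reflects detection

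*Protocol article*

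**What the plan says.** The Secondary outcomes section of the protocol article lists "AEs and postoperative complications using the Clavien–Dindo Classification", and the Secondary objectives give the schedule: "AEs and postoperative complications at 6-weeks 3-, 6- and 12-months postrandomisation". Neither section sets a different schedule for either arm.

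The section Safety reporting, AEs and SAEs adds a collection window, "AEs and SAEs will be collected from the point of randomisation up to 12 months", and an awareness trigger for serious events: "SAEs will be reported to WCTU within 24 hours of research staff becoming aware of the event". The Safety outcomes section narrows what is recorded: "AEs and serious adverse events (SAEs) related to the trial postconsent will be recorded on the appropriate CRF". It leaves out treatment events from concomitant care such as chemotherapy or radiotherapy, and persistent pain without new pathology.

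The arms differ in trial-delivered contact after discharge. The GRRAND programme consists of "up to six, 1-hour outpatient appointments" over 6 months, and further sessions are permitted where clinically indicated. For controls, "No routine outpatient or follow-up physiotherapy will be provided". The section Concomitant recovery treatments lets participants in either arm see a GP, physiotherapist or other professional, and records this through the health utilisation questionnaire.

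**The concern.** A between-arm comparison of AEs is fair only if an event has the same chance of being recorded in either arm. Here one arm has repeated sessions of up to an hour with a trial-trained physiotherapist, in which the participant's neck, shoulder and general recovery are discussed. Events that a control participant might forget or not mention at a scheduled follow-up may be raised at such a session. With an open collection window and a reporting trigger based on awareness, such events could be counted in one arm only.

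Two things are at stake. An excess in GRRAND caused by detection could be read as harm from the programme. A real excess could be dismissed as detection, because the data would not show which it was. AE and serious AE (SAE) data go to the oversight committees, and the End of trial section allows early stopping after their recommendation, so the question matters during the trial as well as at the final analysis.

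**Working it through.** **The plan's own figures.** The article gives no AE rate, no detection rate and no power for AEs, so there is no AE figure to reproduce. The only figure used below is the group size: 292 / (1 − 0.25) = 389.3, rounded up to 390, or 195 per group, as stated under Power and sample size.

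**Occasions for detection within the trial, from the text.**

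| Source | GRRAND | Control |
|---|---|---|
| Scheduled AE time points (6 weeks, 3, 6, 12 months) | 4 | 4 |
| Trial-delivered physiotherapy sessions after discharge | up to 6, more permitted | 0 routine |
| Total | up to 10 or more | 4 |

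This takes the planned maximum for GRRAND and omits contacts outside the programme, which both arms may have. Three of the four common time points fall in the first 6 months, which is also when the sessions are planned. Between 6 and 12 months the arms have similar contact unless extra sessions are given.

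**Illustration with assumed detection.** Let the true risk p be equal in both arms. Assume that the scheduled time points pick up 70% of events in both arms and that sessions pick up half of the rest in GRRAND.

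- Detection in GRRAND = 0.70 + 0.5 × 0.30 = 0.85
- Recorded risk, control, p = 15%: 0.15 × 0.70 = 0.105, or 20.5 of 195
- Recorded risk, GRRAND, p = 15%: 0.15 × 0.85 = 0.1275, or 24.9 of 195
- Odds ratio = (0.1275 / 0.8725) / (0.105 / 0.895) = 1.25
- With p = 10% the odds ratio is 1.23; with p = 20% it is 1.26

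**Range.** With equal true risk, the recorded risk ratio is detection in GRRAND divided by detection in control. The last column is the chance of a nominally significant excess in GRRAND (195 per arm, two-sided 5%, normal approximation); without bias it would be 2.5%.

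| Assumed detection, GRRAND / control | Risk ratio | Difference at p = 20% | Chance of significant excess at p = 20% |
|---|---|---|---|
| 0.95 / 0.90 | 1.06 | 1 point | 4% |
| 0.90 / 0.80 | 1.125 | 2 points | 8% |
| 0.90 / 0.70 | 1.29 | 4 points | 19% |
| 0.90 / 0.60 | 1.50 | 6 points | 38% |

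If only events elicited in the same way at the common time points are compared, so that detection is equal in the two arms, the ratio is 1.00.

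**The case against.** The strongest reply is that the article never says session findings are AE data. The intervention case report forms are listed under process evaluation, where the checks named are of session number and duration. SAE reporting depends on awareness by research staff, and the treating physiotherapists are not said to be research staff. A collection window is not in itself a second method of ascertainment; the four time points could fill it. A reader might infer that the plan combines scheduled and session-derived events in one outcome, or that the comparison is already biased. The text supports neither: it does not state the combination, and it does not rule it out.

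A reader might also infer that controls have no outpatient contact, or that the 6-to-12-month gap weakens ascertainment in controls alone. Neither holds. Only routine outpatient physiotherapy is withheld, and the late gap is largely shared by both arms.

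The restriction to trial-related events and the exclusions under Safety outcomes remove some events likely to be mentioned at a session. The restriction can also act the other way, because controls have no trial-delivered outpatient treatment to which an event could be attributed.

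Finally, the article is condensed. It refers AE management to the trials unit's standard operating procedure, the assessment schedule to a supplement and the analysis to the SAP, so equal ascertainment may already be specified there. That stands as a reason for modest confidence. It does not dispose of the point, because an SAP can separate events by source only if the source was recorded when the event was collected.

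**Conclusion.** The concern holds as a possibility, not as a demonstrated bias. The design gives one arm more trial-linked occasions on which events can come to light, mainly in the first 6 months, and nothing in the article confines the between-arm comparison to the common time points or marks events first noted at a session. If such events enter the data, the expected direction is more recorded events in GRRAND.

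The size is unknown. The odds ratio of 1.25 and the risk ratios of 1.06 to 1.50 rest wholly on assumed detection fractions and an assumed equal true risk. On the 15% illustration, a significant excess would appear only about 10% of the time, so the likelier harm is a safety table that is hard to interpret rather than a false positive test. The SPADI primary outcome is not affected. The change is worth making while data are being collected, with medium confidence given what the full protocol may already contain.

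**What to change.** 1. Add a field to the AE form for how each event came to light: scheduled time point, physiotherapy session, or other.
2. State in the protocol or SAP that the main between-arm comparison of AEs and complications uses events elicited with the same questions in both arms at 6 weeks and 3, 6 and 12 months.
3. Report all events alongside that comparison, to the Data Monitoring Committee and in the results, with those first noted at a session listed separately.
4. Leave expedited SAE reporting as it is.

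The cost is one form field and a sentence or two of text. The field should be added early, since the source of events already collected may not be recoverable. The small downside is that events known only from a session leave the main comparison, although they are still reported. If the full protocol or the trials unit's procedure already provides for this, a sentence confirming it is enough.

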### Power and sample size

Based on the feasibility study’s data,^23^ using our primary outcome of the SPADI at 12-month follow-up, to show a worthwhile difference of eight points with 90% power and 5% level of significance with an SD of 21.1,^44^ we need data on 292 participants. Allowing for 25% loss to follow-up, a total of 390 participants (195 in each group) will be required with an allocation ratio 1:1. We will require a total of 17 physiotherapists, each with an average of 12 patients to deliver the intervention. The loss to follow-up over 12 months has been modelled on 25% based on the previous literature^45^ and a greater proportion of participants in this trial being assessed at 12 month compared with our feasibility study.^23^ We will be striving to achieve a follow-up rate of >75%.

### Internal pilot

The first 6 months of randomisation will be an internal pilot, with a green target of 40 randomised. The pilot will take place in a minimum of four hospitals, selected to offer diversity across the population while also representative of centres/physiotherapists that will take part in the main trial. The progression criteria are presented in table 1.

**Table 1 T1:** Stop–go criteria for internal pilot

Red	Amber	Green
N participants recruited	≤26 (<66%)	27–39 (66%–99%)	≥40 (100%)
Recruitment rate/site/month	< 1 participant	1–2 participants	3 participants
Number of sites opened	1 site	2–3 sites	4 sites
Intervention session attendance*†	≤27 (<70%)	28–39 (≥70%–<99%)	≥40 (100%)
Loss to follow-up†	≥10 (>25%)	1–9 (1%–25%)	0 (0%)

* Minimum one assessment and three follow-up appointments (four sessions in total) or if patient–physiotherapist goals met and agreed discharge made prior to this session number.

† Analysed at 12-month follow-up of the cohort randomised in first 6 months to obtain sufficient data.

If the internal pilot meets amber criteria, we will consult the funder, inform the TSC, review processes, look to open additional sites or amend trial processes and review again in 6 months. If the red criteria are met across all indicators, we will discuss stopping the trial with the TSC and funder.

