## Methods and analysis

### Trial design

GRRAND is a multicentre, pragmatic randomised controlled trial with 1:1 allocation, integrated health economic evaluation and process evaluation. The trial will include a 6-month internal pilot to test detailed trial procedures, data collection and confirm the feasibility of recruitment and conduct. Participants will be followed over 12-months postrandomisation to assess shoulder function, HRQoL, adverse events (AEs) and to collect cost data for economic evaluation. The trial will be conducted in NHS hospital settings. Sites will be selected to reflect demographic and socioeconomic diversity. Priority will be given to sites serving areas with high proportions of ethnic minority populations (especially Black communities) and areas of socioeconomic deprivation, including coastal communities.

This protocol article was written following the Standard Protocol Items: Recommendations for Interventional Trials guidelines.^24^
Figure 1 is the participant flow diagram. The participant consent form is presented (online supplemental file 1). A summary of core trial information is presented in the WHO trial registration dataset (online supplemental file 2).

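### Pilot attendance counts in Table 1 are scaled to all 40 randomised, but only about 20 can attend, so count and percentage contradict each other at the recruitment target

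*Protocol article*

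**What the plan says.** All of this is in the protocol article.

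- **Pilot size.** Internal pilot: "The first 6 months of randomisation will be an internal pilot, with a green target of 40 randomised". The recruitment row of Table 1 is red at ≤26, amber at 27–39 and green at ≥40.
- **Attendance bands.** Table 1, attendance row: red ≤27 (<70%), amber 28–39 (≥70%–<99%), green ≥40 (100%).
- **Who counts as an attender.** Table 1 footnote: "Minimum one assessment and three follow-up appointments (four sessions in total) or if patient–physiotherapist goals met and agreed discharge made prior to this session number". The unit is therefore a participant, not a session.
- **Cohort and timing.** Second footnote, which applies to attendance and to loss to follow-up: "Analysed at 12-month follow-up of the cohort randomised in first 6 months to obtain sufficient data".
- **Allocation.** Trial design: "GRRAND is a multicentre, pragmatic randomised controlled trial with 1:1 allocation". Randomisation and blinding: "Randomisation will use a variable block size and will be 1:1 using minimisation".
- **Who has sessions.** The outpatient programme is described only under Group 1. For the comparator, Group 2 says: "No routine outpatient or follow-up physiotherapy will be provided as per current, best, usual NHS care".
- **Use of the criteria.** The Internal pilot section foresees a discussion about stopping, with the steering committee and the funder, only when every indicator is red.

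**The concern.** Attendance at programme sessions is an outcome that only one arm can have. The counts in the attendance row nevertheless run up to 40, the same number as the two-arm recruitment target. If the counts were set on the total pilot, they ask for about twice as many attenders as the design can supply.

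Attendance is the only row in Table 1 that measures delivery of the intervention. If its counts cannot be reached at the planned pilot size, it cannot do the job it was put there for, and whoever scores the table must choose between a count and a percentage that disagree.

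**Working it through.** **Inputs.** Pilot target 40 in total (Internal pilot). Allocation 1:1 by minimisation (Trial design; Randomisation and blinding). Attendance bands ≤27, 28–39 and ≥40 (Table 1). Programme sessions in the GRRAND arm only (Groups 1 and 2).

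**Step 1: reproduce the plan's percentages.** Dividing each printed count by 40:

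| Count | Count / 40 | Printed label |
|---|---|---|
| 27 | 67.5% | <70% |
| 28 | 70.0% | ≥70% |
| 39 | 97.5% | <99% |
| 40 | 100% | 100% |

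The row is consistent on a denominator of 40, which is the total pilot target.

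**Step 2: how many can attend.** 40 × 1/2 = 20 in the GRRAND arm. Minimisation keeps the arms close to equal. Even under simple 1:1 randomisation, the probability that 28 or more of 40 fall in one arm is 0.0083, or 0.8%; under minimisation it would be smaller.

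**Step 3: score perfect attendance at the target.** The count is 20, and 20 ≤ 27, so the row is red. As a percentage of those who could attend, 20/20 = 100%, so the row is green. At this pilot size every possible result, from 0 to 20 attenders, is red by count.

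**Step 4: what the printed counts would require.** With every GRRAND participant attending:

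- amber needs 28 in the arm, so 28 × 2 = 56 randomised;
- green needs 40 in the arm, so 40 × 2 = 80 randomised, twice the recruitment target.

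Table 1's own green figures for rate and sites give 3 per site per month × 4 sites × 6 months = 72 randomised if all four sites recruit for the full period. That is 72/2 = 36 in the arm, which is amber by count at best.

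**Step 5: link with the recruitment row.** Recruitment is red at ≤26. The number of attenders cannot exceed the number randomised, and 26 ≤ 27, so attendance by count is then red whatever the allocation and however good the attendance.

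**Step 6: the same percentages on the right denominator.** For 20 allocated, 0.70 × 20 = 14. The bands become red ≤13, amber 14–19 and green 20.

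**The case against.** **The practical consequence is limited.** A reader might infer that a fully successful pilot would be judged a failure, or that this row could stop the trial in error. The document does not support that. Stopping is discussed only if all five indicators are red, and even then the outcome is a discussion. At 40 randomised the recruitment row is green, so the all-red condition cannot be met. The row is also read at 12-month follow-up, which for the last pilot participants is about 6 + 12 = 18 months after randomisation begins, so it cannot drive a decision when the 6-month pilot closes. This objection stands in full.

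**The percentages are sound.** Taken over those allocated to GRRAND, the 70% and 100% cut-offs separate good attendance from poor. This also stands: the defect lies in the counts and in their conflict with the percentages, not in the cut-offs.

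**A larger pilot could leave red.** This is true from about 56 randomised. A reader might infer that any successful pilot would be red by count; that holds only near the target of 40.

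**Other readings of the row.** None repairs it.

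- If the counts were sessions, 20 participants × 4 sessions = 80, not 40.
- If 40 meant the programme arm, the article would have to say so. Instead the footnote ties the row to everyone randomised in the first 6 months, for whom the target is 40 in total.
- Control participants may obtain physiotherapy elsewhere, since the trial does not restrict other treatment, but that is not attendance at the intervention sessions that the row counts.

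**Conclusion.** The attendance counts are wrong as printed: they use the two-arm total for an outcome confined to one arm. At the recruitment target, full attendance gives about 20, red by count and green by percentage. Amber by count needs about 56 randomised and green about 80, even with perfect attendance.

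The row cannot by itself trigger a discussion about stopping. What is lost is information. Near the target the count cannot distinguish full attendance from none. When recruitment is red, the attendance count is red automatically, so good attendance can never weigh against the all-red rule, which in effect rests on one indicator fewer.

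The conclusion assumes near-equal arms, which minimisation supports, and that the printed counts are applied as they stand. The main-trial sample size and the primary analysis do not use this row and are unaffected. The loss-to-follow-up row applies to both arms, so a denominator of 40 is appropriate there.

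**What to change.** Define the attendance row as the percentage of pilot participants allocated to GRRAND who meet the footnote's definition. Keep the stated percentage bands: red <70%, amber 70% to <100%, green 100%. Writing the upper amber limit as <100% rather than <99% only closes the gap below green. Let the counts follow the actual number allocated, with the 20-participant case as an illustration: red ≤13, amber 14–19, green 20.

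The cost is a correction to one row of a table and its footnote, with no extra data or participants. It should be made before the pilot cohort's attendance is assessed, so that the bands are not reinterpreted once the result is known.
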